### Statistical Analysis

The primary endpoint (change in the C-SSRS IoI-subscale score between baseline and 3 months) will be compared between the 2 arms using the constrained longitudinal data analysis model (cLDA) proposed by Liang and Zeger [37]. In the cLDA, both the baseline and postbaseline values are modeled as dependent variables using a linear mixed model, and the true baseline means are constrained to be the same for the 2 treatment arms. Hence, the cLDA provides an adjustment for the baseline values in estimating the treatment effects. The treatment effect will be estimated by the time-by-arm interaction, including gender as a covariate.

The secondary binary endpoints at 3 months will be compared between the 2 arms using logistic regression models adjusted for gender. Odds ratios and their 95% CI values will be derived from logistic regression models as effect sizes (experimental vs control). The secondary quantitative endpoints will be compared between the 2 arms using analysis of covariance to adjust for baseline score and gender. Standardized mean differences and their 95% CI values will be calculated as the effect size. If the model residuals are not distributed normally (despite the log-transformation of the data), analysis of covariance will be performed on the rank-transformed data (nonparametric analysis).

Finally, the variables related to the use of the platform will be described in the intervention group. These quantitative variables will be expressed as mean (SDs), median (IQR), and ranges.

Statistical tests will be performed with a 2-tailed alpha risk of 0.05. No adjustment for multiple testing will be applied, and thus, all secondary objectives will be considered exploratory. All analyses will be performed in all randomized patients based on their original group of randomization, according to the intention-to-treat, after handling missing values.

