### Study Design

ORIAS is a randomized, controlled, single-center, open-label, 2-arm, superiority trial with balanced parallel groups. The participant pathway through the study is illustrated in Figure 2. This trial was designed and reported in accordance with the SPIRIT (Standard Protocol Items: Recommendations for Interventional Trials) guidelines. For the complete checklist, refer to Multimedia Appendix 1.

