**Figure 2 figure2:**
[figure not shown]
Overview of participant pathway through the Online Referral and Intervention to Prevent Adolescent and Young Adult Suicide protocol.

The ELIOS system is promoted through organic and paid SM campaigns, enabling distressed adolescents and young adults to initiate contact spontaneously via its Facebook Messenger account. Upon receiving a first-contact private message, an algorithm-driven smartbot automatically responds through the same channel to begin the interaction. The smartbot verifies whether this is the user’s initial contact, acknowledges their effort in seeking help, and invites them to click a hyperlink to access the ELIOS website. Importantly, the smartbot’s preregistered messages were developed based on input from the focus group of adolescents and young adults.

Once on the website, users are guided through a sequence of pages where they (1) receive comprehensive information about the program and research study, (2) complete an online eligibility assessment form, and (3) if eligible, are invited to provide electronic informed consent. Upon consenting, users proceed to complete online questionnaires for the study’s baseline assessment (M0). Finally, participants are randomly assigned to 1 of 2 study groups. The randomization procedure involves block randomization stratified by sex, with randomly generated blocks of size 4. A random selection among the possible block compositions is then used to generate the final allocation list.

Participants assigned to the control group are directed to a final webpage containing a list of first-line, specialized, and emergency mental health resources, including general practitioners, psychiatric outpatient clinics, emergency services, and the national suicide prevention helpline. The resources are tailored to the participant’s level of suicidality, as assessed through the inclusion forms. This comparator was selected to minimize intervention effects while still providing access to the most reliable mental health resources available online.

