### Endpoints

The intensity of suicidal ideation is measured at baseline (M0) and at 3 months (M3). It is assessed using the Intensity of Ideation (IoI) subscale of the Columbia Suicide Severity Rating Scale (C-SSRS) [33]. This subscale comprises 5 items. Participants evaluate different dimensions of their most severe suicidal thoughts during a given period: frequency, duration, controllability, deterrents,and reason for ideation. Each item is rated on a 0 to 5 (controllability, deterrents, and reasons for ideation) or 1 to 5 Likert scale (frequency and duration).

Scores are summed to yield a total ranging from 2 to 25, with higher scores indicating greater intensity of suicidal ideation. The IoI subscale has demonstrated good internal consistency (Cronbach α between 0.73 and 0.95) [33]. The French version used in this study has undergone linguistic validation [34].

All secondary endpoints in both groups are assessed at month 3 (M3) using self-administered questionnaires. Participants are asked: (1) whether and when they consulted a general practitioner, psychiatrist, psychologist, or nurse, or whether they were admitted to a hospital or emergency department for psychological, psychiatric, or substance use-related reasons; (2) whether the consultation or admission was preceded by a suicide attempt or life-threatening behavior; (3) whether and when they attempted suicide without seeking care from conventional mental health services or visiting an emergency department.

Vital status will be determined after the end of the study by querying the Registers of Civil Status, using participants’ identity and place of birth.

Attitudes toward mental health care are assessed using a French version of the Attitudes Toward Seeking Professional Psychological Help–Short Form (ATSPPH-SF) [35]. The ATSPPH-SF is one of the most widely used tools for evaluating attitudes related to help-seeking. It consists of 10 items rated on a 4-point Likert scale from disagree to agree. For 5 items, strong agreement indicates more positive attitudes, while for the remaining 5 items, strong agreement reflects more negative attitudes. We reversed the scoring scale for these latter 5 items so that, overall, a higher ATSPPH-SF score corresponds to a more positive attitude toward seeking help.

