### Required Sample Size

According to the results from Nam et al [38], we assume that the 3-month mean score at the C-SSRS lol-subscale will be 9.8 (SD 5.4) in the control arm. In the ELIOS intervention arm, we expect this value to be decreased by 20%, corresponding to a mean difference of 2 points at 3 months. With an SD of 5.4 points, a type I error of 5%, and a power of 90%, we calculated that 154 patients per arm will be required to detect a difference of 2 points in the primary endpoint with a 2-sided *t* test. To account for an anticipated loss to follow-up rate of 20%, we will enroll 193 participants per group, which means a total of 386 participants.

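### Binary secondary endpoints are adjusted for gender only; prespecifying baseline ideation intensity as well would be a cheap, modest improvement to a model that is already valid

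*Protocol article*

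**What the plan says.** Under Statistical Analysis, the protocol article fixes the covariates of the binary secondary models: "The secondary binary endpoints at 3 months will be compared between the 2 arms using logistic regression models adjusted for gender". In the same section the primary model takes the baseline IoI score as part of the outcome vector, with the baseline means constrained to be equal across arms. Quantitative secondary endpoints are analysed by covariance analysis with the baseline score and gender. Only the binary endpoints carry no baseline severity measure.

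The measure is available. Under Endpoints: "The intensity of suicidal ideation is measured at baseline (M0) and at 3 months (M3"). Under Study Design, in the text after Figure 2, "Upon consenting, users proceed to complete online questionnaires for the" baseline assessment, and allocation comes afterwards. Sex is the stratification factor: "The randomization procedure involves block randomization stratified by sex".

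Three further statements limit the point. All secondary objectives are declared exploratory, without multiplicity adjustment. Only the primary endpoint is sized. Analyses are to include everyone randomized, by intention to treat, once missing values have been handled; the article does not name the method.

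**The concern.** Suicide attempts, care contacts and admissions have no baseline value of their own in the plan, so the rule of adjusting for one's own baseline gives these models nothing beyond gender. A pre-randomization measure of suicidality is a natural candidate for that role. Two things could be at stake.

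- **Precision.** If IoI predicts the outcome, leaving it out costs some power.
- **Dropout.** The article expects 20% loss to follow-up in an open-label trial where one arm has continuing clinician contact and the other receives a web page. If loss depends on baseline severity, and does so differently by arm, a gender-only comparison of the observed outcomes is biased. A model that includes IoI is protected against this when dropout depends only on IoI and arm.

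**Working it through.** **1. The plan's own figure.** Inputs from Required Sample Size: difference 2 points; "With an SD of 5.4 points, a type I error of 5%, and a power of 90"%; control mean "will be 9.8 (SD 5.4) in the control arm".

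- n per arm = 2(1.960 + 1.282)² × 5.4² / 2² = 153.2, rounded up to 154. Solving for the t test gives 154.2, with 89.97% power at 154.
- 154 / (1 − 0.20) = 192.5, rounded up to 193 per arm, 386 in total.

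The stated size reproduces. It concerns the primary endpoint only.

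**2. Power with and without IoI.** The article gives no event rates and no association between IoI and any binary endpoint, so both are assumed and shown as ranges. Setting: 154 completers per arm, 1:1, two-sided 0.05, Wald test, 3,000 simulated trials per cell. Each cell shows power (%) with gender only → with IoI added.

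| Assumed risk, control vs ELIOS | IoI OR 1.5 per SD | IoI OR 2.0 per SD | IoI OR 3.0 per SD |
|---|---|---|---|
| 5% vs 2.5% | 13.6 → 13.6 | 13.9 → 14.6 | 13.5 → 15.1 |
| 10% vs 5% | 38.2 → 38.4 | 36.8 → 37.4 | 36.5 → 39.5 |
| 15% vs 7.5% | 54.3 → 55.9 | 55.3 → 58.2 | 54.7 → 60.0 |
| 20% vs 10% | 70.8 → 71.2 | 69.7 → 72.2 | 69.3 → 74.8 |
| 40% vs 55% (care access) | 75.9 → 77.5 | 75.4 → 79.2 | 74.3 → 83.6 |

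Monte Carlo error is up to √(0.5 × 0.5 / 3000) = 0.9 points per figure; the paired differences are more precise. With a non-prognostic IoI (OR 1.0), the change lies between −0.5 and +0.3 points, which is noise. At OR 1.5 to 2.0 the gain is 0 to 3.8 points. At attempt risks of 5% to 10% it is below 1 point.

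**3. Validity without differential dropout.** With no treatment effect and IoI OR 2.0, rejection rates were 3.4% to 5.3% for gender only and 3.6% to 5.4% with IoI. Both models hold the 5% level.

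**4. What changes in the estimate.** At 20% vs 10% and OR 3.0, the median log odds ratio moved from −0.82 to −0.97 and its standard error from 0.34 to 0.37. The adjusted odds ratio is a different, conditional quantity, and power rises although the standard error does too.

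**5. Dropout that differs by arm.** Assumptions: 193 per arm, 20% dropout in each arm, no true effect, observed outcomes analysed, 2,000 trials per setting.

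- Dropout rises with severity in controls only (log-odds 0.7 per SD), IoI OR 2.0: the gender-only odds ratio is 1.10 at 15% risk and 1.08 at 50% risk. With IoI it is 1.00.
- Opposite slopes in the two arms, IoI OR 2.0: the gender-only odds ratio is 1.18, with type I error 7.6% (15% risk) and 11.6% (50% risk). With IoI the odds ratio is 1.00 and the error 5.1% and 6.0%. A repeat with another seed and slopes of ±0.7 gave 7.2% and 9.6% for gender only, and 5.5% and 4.6% with IoI.
- The same slope in both arms: no bias from either model.

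**6. Sparse events.** At 10% vs 5%, expected events are 154 × 0.10 + 154 × 0.05 = 23.1. That is 23.1 / 2 = 11.6 per covariate with arm and sex, and 23.1 / 3 = 7.7 once IoI is added.

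**The case against.** The strongest reply is that nothing here is wrong. Arm plus the counterpart of the stratification factor is a proper prespecified model. The endpoints are exploratory, no power is claimed for them, and preferring another covariate is a matter of taste. That stands as a reason not to call this an error. It does not remove the case for a cheap change in a section that uses baseline values everywhere else.

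A reader might infer more than the article supports:

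- **That IoI is known to be prognostic.** No association is given, and everyone enrolled had ideation in the week before contact, so even the spread of IoI is unknown.
- **That IoI drives the tailoring of control resources or the clinicians' contact list.** The article speaks there of suicidality from the inclusion forms, or of suicidality scores and waiting time. It does not name IoI.
- **That a complete-case analysis is planned.** The article says the opposite in outline: all randomized participants, after missing values are handled. An imputation model containing IoI would give much of the protection shown in step 5.
- **That power is lost at no cost, above all for suicide attempts.** The gain is smallest there. The change alters the effect measure and, by step 6, adds strain when events are few.

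**Conclusion.** The point holds as a low-cost improvement. The binary models omit a baseline measure that is collected before randomization, while the neighbouring analyses use baseline values. The gender-only model remains valid.

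The precision benefit is about 0 to 4 power points at an assumed IoI odds ratio of 1.5 to 2.0 per SD. It is greater for common outcomes such as care access and near zero for rare attempts, which stay at roughly 14% to 40% power with or without the covariate under the assumed halving of a 5% to 10% risk. Gains above 5 points appear only at OR 3.0.

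The dropout benefit is conditional on three things: loss depends on baseline severity, it does so differently by arm, and the unspecified missing-data handling does not already use IoI. The expected 20% loss is in the article; the dropout slopes and all event rates and associations used here are assumptions.

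**What to change.** Before outcome data by arm are seen, state in the analysis plan that each binary secondary endpoint with enough events is modelled by logistic regression with arm, sex and baseline IoI as a continuous covariate. Set the event threshold in advance and apply it to the count pooled over arms; below about 10 events per parameter, use Firth penalisation. Do not force covariates on an endpoint with almost no events, as all-cause mortality may prove to be. Keep the gender-only model as a sensitivity analysis.

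The cost is one sentence and one covariate already collected. The odds ratio becomes conditional on IoI as well as sex and should be labelled so, and one more parameter is fitted when events are few. The timing matters: the article puts the start of analysis in April 2026, and the choice is credible only if dated before then.

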### Required Sample Size

According to the results from Nam et al [38], we assume that the 3-month mean score at the C-SSRS lol-subscale will be 9.8 (SD 5.4) in the control arm. In the ELIOS intervention arm, we expect this value to be decreased by 20%, corresponding to a mean difference of 2 points at 3 months. With an SD of 5.4 points, a type I error of 5%, and a power of 90%, we calculated that 154 patients per arm will be required to detect a difference of 2 points in the primary endpoint with a 2-sided *t* test. To account for an anticipated loss to follow-up rate of 20%, we will enroll 193 participants per group, which means a total of 386 participants.

### Ethical Considerations

Participation in the ORIAS study was contingent upon the signing of informed consent by all participants. As compensation for their participation, they received a €20 (US $23) digital gift voucher. Required measures have been implemented under the supervision of the data protection officer of the CHU de Lille to ensure compliance with the General Data Protection Regulation guidelines. Only data that are strictly necessary for the research purposes, as predefined in the authorized protocol, are collected. All data are gathered via the secure ELIOS platform or website. Access to individual-level information stored on the platform is restricted to authorized web-clinicians and protected by personal, 2-factor–authenticated, password-secured accounts. Data can be extracted by the research team only in anonymized form, ensuring that all analyses are conducted on fully anonymous datasets. All data are hosted on a dedicated, secure virtual private health data server at the CHU de Lille, France. Based on these measures, the ORIAS study was approved by the Sud-Ouest and Outre-Mer IV Committee for the Protection of Persons (IORG0009855) and authorized by the French Data Protection Authority (Commission Nationale de l’Informatique et des Libertés). The trial was registered on ClinicalTrials.gov under the identifier NCT04642157.

## Results

The ORIAS study was funded in November 2018, and data collection began on October 12, 2022. As of December 2025, a total of 375 participants had been enrolled, 190 in the intervention group and 185 in the control group, representing 97% of the required sample size. Overall, 50% (187/375) of participants were male (87/190, 46% in the intervention group and 100/185, 54% in the control group). The mean age was 21.6 (SD 2.3) years in the overall sample (intervention: 21.7, SD 2.4 years; control: 21.5, SD 2.33 years). Due to irregular enrollment rates, participant recruitment is expected to conclude in April 2026. Data analysis will be conducted between April 2026 and the end of 2026, and the first publication is anticipated in early 2027. No deviations from the registered protocol were observed.

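### The reported enrolment by sex and arm cannot arise from the stated sex-stratified blocks of 4; the article does not show which statement is wrong, so the two must be reconciled

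*Protocol article*

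**What the plan says.** The Study Design part of the Methods gives the design as follows: "ORIAS is a randomized, controlled, single-center, open-label, 2-arm, superiority trial with balanced parallel groups". The text after Figure 2 gives the allocation method: "The randomization procedure involves block randomization stratified by sex, with randomly generated blocks of size 4". It adds: "A random selection among the possible block compositions is then used to generate the final allocation list". There is one centre, and no stratification factor other than sex is named.

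The Results section states that as of December 2025 "a total of 375 participants had been enrolled, 190 in the intervention group and 185 in the control group", and that of these half of the "participants were male (87/190, 46% in the intervention group and 100/185, 54% in the control group". The same paragraph ends: "No deviations from the registered protocol were observed".

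The Statistical Analysis section adjusts the primary and secondary models for gender and defines the analysis set: "All analyses will be performed in all randomized patients based on their original group of randomization". The article mentions no exclusion after randomisation and no change of allocation method.

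**The concern.** Stratified permuted blocks keep the arms close within each stratum at every moment of recruitment. The reported arms are far apart within each sex, in opposite directions, and their totals also differ by more than the method permits. The bound is deterministic, so chance cannot account for the difference.

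Two things are at stake. First, the final report may describe an allocation procedure that is not the one that operated. Second, if people were taken out of the counts after allocation, the planned analysis of everyone randomised may already be incomplete. This is an open-label trial with self-reported outcomes, so a reader will rely heavily on the allocation being as described.

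**Working it through.** **Inputs.** Block size 4, stratified by sex (Methods, Study Design). 1:1 ratio, one centre (same section). 190 intervention and 185 control; males 87 and 100 (Results). Non-males by subtraction: 190 − 87 = 103 and 185 − 100 = 85.

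**Internal consistency of the counts.** 87 + 100 = 187; 87/190 = 45.8%; 100/185 = 54.1%; 187/375 = 49.9%; 375/386 = 97.2%. All agree with the printed figures, so no obvious single-digit misprint explains the problem.

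**Bound.** A balanced block of 4 has 6 possible orders of two and two. A completed block contributes no difference, and at most one block per stratum is open at any time. The largest difference inside an open block is 2. Hence the maximum is 2 per sex, and 2 × 2 = 4 overall with two strata.

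**Bound at the reported sizes, each list used in order.** 187 = 46 × 4 + 3, so males must differ by exactly 1. 188 = 47 × 4, so non-males must differ by 0. The total must then differ by 1.

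| Group | Intervention | Control | Reported difference | General maximum | Value at these sizes |
|---|---|---|---|---|---|
| Male | 87 | 100 | 13 | 2 | 1 |
| Non-male | 103 | 85 | 18 | 2 | 0 |
| All | 190 | 185 | 5 | 4 | 1 |

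A within-stratum difference of 13 would need blocks of at least 26, and one of 18 would need blocks of at least 36.

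**Can a sex/gender mismatch explain it?** Moving people between sex categories leaves the arm totals unchanged, and 5 exceeds 4. With two strata, relabelling alone therefore fails.

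**Can a third sex category explain it?** The overall maximum becomes 3 × 2 = 6, so a total difference of 5 is possible (2 + 2 + 1). The male stratum is still limited to 2, and the pooled non-males to 4. If relabelling is added, a total of 5 requires every stratum to favour intervention by at least 1, because the other two supply at most 4. The male difference would then have to move from at least 1 towards intervention to 13 towards control. That is a net shift of at least 14 people.

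**Can removals after randomisation explain it?** Assume two strata and that reported sex is the stratifier.

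- Males: adding 10 to intervention gives 97 versus 100, difference 3, which is too large. Adding 11 gives 98 versus 100, or 198 = 49 × 4 + 2, where a difference of 2 is possible.
- Non-males: adding 16 to control gives 103 versus 101, or 204 = 51 × 4, which must split 102:102, so it is impossible. Adding 17 gives 103 versus 102, or 205 = 51 × 4 + 1, where a difference of 1 is possible.
- Minimum: 11 + 17 = 28 people out of 375 + 28 = 403, or 6.9%.

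**Is the split unusual under unrestricted 1:1 allocation?** Exact two-sided binomial p-values are 0.38 (87 of 187), 0.21 (103 of 188) and 0.84 (190 of 375). For sex by arm, chi-square = 375 × (87 × 85 − 100 × 103)² / (187 × 188 × 190 × 185) = 2.56, p = 0.11. It is not unusual.

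**The case against.** The strongest reply is that the Results paragraph is a short interim snapshot, not an analysis table, and its tallies by arm or sex may simply be wrong. The article also stratifies by sex but adjusts for gender and never gives the number of categories, so the reported variable may not be the stratifier. Both points stand as possible causes. They do not remove the conflict: a wrong tally is itself an error to correct, and a different sex variable cannot alone produce the total under two strata.

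A reader might go further and infer that the randomisation failed, that the website's software is faulty, or that the causal comparison is compromised. The article does not support this. The split is what simple randomisation would often give. If stratification or blocking lapsed while allocation stayed random, the arms remain a randomised comparison, and gender is already in the models. What would be lost is balance by design and an accurate account of the method.

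Nor can the no-deviations sentence be called false on this evidence. It refers to the registered protocol, which is not shown and may specify the allocation differently. It does sit beside counts that the article's own method excludes, so it needs checking.

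**Conclusion.** The stated allocation method and the stated counts cannot both hold. The differences are 13, 18 and 5, against maxima of 2, 2 and 4. This rests on balanced 2:2 blocks, one list per sex used in order, two sex strata, and reported sex being the stratifier. A third category relaxes only the total and the pooled non-male limit, and leaves both within-sex gaps impossible.

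Confidence is high in the incompatibility and low in any particular cause. The candidates are the description, its implementation, the counts or the sex variable behind them, and missing randomised participants, alone or in combination. Bias in the treatment effect is not shown. The point still has to be resolved before analysis, because one of the candidate causes bears on the intention-to-treat set and every one of them requires a correction to something stated or done.

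**What to change.** Before database lock, reconcile the allocation list (stratum, block, sequence, time stamp) with every allocation the website issued, and both with the counts in the Results. A statistician outside the trial team would be well placed to do it. Then act on what is found:

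- If the tallies or the sex variable are wrong, correct the counts and state which variable was the stratifier.
- If a different procedure operated, describe that procedure and revise the no-deviations statement as needed.
- If the implementation is found faulty, repair it for any participants still to be enrolled (386 − 375 = 11 at the December 2025 report date).
- If anyone was removed after randomisation, restore them to the intention-to-treat set and report the number by arm.

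In every case keep sex in the models as a covariate, and do not claim balance by design unless the audit confirms it. The cost is a few days of audit, corrected wording and, where needed, a deviation note. No extra participants are required.
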